### Acceptability and feasibility

To evaluate the acceptability and feasibility of our intervention, we will employ an explanatory sequential mixed-methods approach. For older adults, we will start by collecting quantitative data through the Acceptability of Intervention Measure (AIM) and Feasibility of Intervention Measure (FIM) Likert scales [41]. Subsequently, we will conduct in-depth interviews with a subset of 16–20 older adults, including those who were both less and more satisfied with the intervention. These interviews aim to delve into the participants’ experiences with the program. During these interviews, we will explore feelings about the intervention, thoughts on the activities facilitated by the CHWs, aspects older adults’ value and find satisfying, as well as areas they believe could be improved.

We will use a convergent mixed-methods approach with CHWs, older adult relatives, and health professionals, combining quantitative scores from the Feasibility and Acceptability Likert scales with in-depth interviews, all within the same phase [42]. This comprehensive approach ensures a holistic interpretation of the data.

Interviews with CHWs will focus on various aspects, including challenges faced while providing the intervention to different older adults, time invested, compensation, self-care practices, and overall satisfaction. In addition to these interviews, we will collect valuable insights during weekly supervision sessions, where a designated note-taker will document CHWs’ experiences and interactions with participants and their families, if applicable.

Interviews with family members will explore their perceptions of mental health care, their acceptance of the intervention, positive changes observed in the family member receiving the intervention, and various other related topics.

Interviews with health professionals will seek to understand their perspectives on the long-term feasibility of the intervention and explore potential avenues for support and collaboration, such as funding opportunities and referrals. This multifaceted approach ensures a thorough examination of the intervention's acceptability and feasibility from multiple perspectives.

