### Study design and sample size

Our study adopts a mixed-method feasibility pilot trial, employing an open-label design with a type 2 implementation-effectiveness focus and featuring two parallel groups. We plan to randomize a total of 64 older adults (60 years and older) stratified by sex and dividing them equally into “control” and “intervention” groups. The decision to include 64 participants was influenced by the availability of pairs of trained CHWs, who will be responsible for delivering the intervention to a group of 32 participants each. The trial is scheduled to run for a duration of 22 weeks from the start of enrollment. For a visual representation of our study design, please refer to Fig. 1.

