### Feasibility of carrying out a larger trial

We will collect feasibility data from the pilot trial, which will allow us to assess and plan a full-scale randomized controlled trial (RCT). A comprehensive overview of these feasibility domains, encompassing quantitative indicators, qualitative data, and predefined success criteria, can be found in Table 2. The qualitative data will be sourced from a variety of avenues, including field notes maintained by the study coordinator and interviews with participants. Special attention will be given to those who chose not to participate or who withdrew from the study. These interviews will allow us to elucidate the underlying reasons and barriers contributing to their decisions, thereby enhancing our understanding of the trial’s feasibility and participant perspectives.

**Table 2 Tab2:** Feasibility assessment for conducting a fully powered randomized controlled trial

Item	Quantitative assessments	Qualitative interviews	Target/criteria for success
Screening	# participants screened/month	Barriers and facilitators to screening and recruitment	
Enrollment	# participants enrolled/month Average time to reach enrollment goal		80% older adults enrolled/4 months
Retention	% older adults who remain in the study in both study groups	Reasons for dropout	80% trial retention at both groups at week-14 75% trial retention at both groups at week-22
Assessments	% of assessment administered as planned	Barriers and facilitators to delivering the intervention	75% evaluations complete

Our progression criteria are not solely based on quantitative success thresholds; instead, we will integrate qualitative data from semi-structured interviews with the quantitative criteria for each domain described in Table 2. For instance, if we do not reach the screening and recruitment targets, we will explore from the fieldworkers' perspectives how we can improve for a future phase. Reasons could include the number of fieldworkers, the way the study is presented, the recruitment strategies, or other factors. In the domain of retention, if a high proportion of participants drop out after being randomized to the control group, we will use the semi-structured interviews to understand their reasons. This feedback may lead us to reconsider the study design, or the type of control used for the future trial.

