### Implementation outcome measures

Implementation outcomes serve as a vital lens through which we can unravel the intricacies of the implementation process, allowing us to pinpoint and address intermediate factors that may impact the success of an intervention within its specific context [39, 40]. These outcomes hold immense significance because they enable us to assess the effectiveness of delivery of VIDACTIVA, paving the way for future research and practice. Without successful implementation, clinical outcomes remain elusive.

To comprehensively evaluate the acceptability, feasibility, and fidelity of the intervention delivery, we will employ mixed methods approaches [37, 38]. A concise overview of the domains, methodologies, and schedule for data collection is provided in Table 3, which offers a clear roadmap for our assessment process.

**Table 3 Tab3:** Evaluation of implementation outcome domains: definition, method, data source, and timeline

Implementation domain	Definition	Method	Data source	Timeline
Acceptability	Extent to which an intervention aligns with an individual’s preferences, needs, and expectations	In-depth interviews Acceptability Likert Scale	Older adults Relatives of older adults Health professionals	week-5, week-14, week-22 week-14 week-14
		Fieldnotes	Supervision sessions	weekly
Feasibility	Practicality of implementation, considering available resources and circumstances	In-depth interviews Feasibility Likert Scale	Older adults Relatives of older adults Health professionals	week-5, week-14, week-22 week-14 week-14
		Fieldnotes	Supervision sessions	weekly
Fidelity	The degree to which an intervention is delivered as intended	Indicators: % of older adults who receive 4 and 8 sessions % of older adults who schedule and do pleasant, social, and physical activities % of older adults who agree to have in-home sessions vs sessions outside % of sessions delivery according to schedule Average time of study visits	Log Study coordinator	Throughout the trial
		Fieldnotes	Supervision sessions	Weekly
		Audio-recording of visits + Checklist	CHWs-Older Adult interaction	Week-6 (Session 5)

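### The week-14 and week-22 AIM/FIM scores describe only older adults still in the study, and the planned withdrawal interviews are not linked to them

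*Protocol article*

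**What the plan says.** - **Schedule of scores.** In Table 3 (Implementation outcome measures) the acceptability and feasibility rows pair in-depth interviews with a Likert scale. Their timeline cell reads "week-5, week-14, week-22 week-14 week-14", that is, three time points for older adults and one each for relatives and health professionals. Weekly supervision fieldnotes are a further source for both domains.
- **Choice of interviewees.** The section Acceptability and feasibility sets out an explanatory sequential design: AIM and FIM first, then "in-depth interviews with a subset of 16–20 older adults, including those who were both less and more satisfied with the intervention".
- **Fidelity.** Table 3 lists indicators that the study coordinator logs for the whole trial, among them the share of older adults who receive 4 and 8 sessions, plus weekly fieldnotes. A single audio recording with a checklist is made at session 5, in week 6.
- **Withdrawers.** The section Feasibility of carrying out a larger trial plans interviews with people who declined or withdrew. Table 2 places reasons for dropout under retention, with targets "80% trial retention at both groups at week-14" and "75% trial retention at both groups at week-22".
- **Analysis.** The Data analysis section gives plain summary statistics for implementation outcomes. The linear mixed model is stated for clinical outcomes only.

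**The concern.** Table 3 defines acceptability as fit with a person's preferences, needs and expectations. Someone who leaves because VIDACTIVA did not fit is direct evidence on that definition. As scheduled, that person contributes no AIM or FIM score after leaving, and none at all if they leave before week 5. Because interviewees are picked by satisfaction after the scales are collected, someone without a score cannot readily be identified as one of the less satisfied.

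The withdrawal interviews would capture such people, but they are described as evidence on the feasibility of a larger trial and are not a Table 3 source for acceptability or feasibility of the intervention. The parts needed are all in the plan but are not joined. Acceptability and feasibility of the intervention are stated aims, and the results are meant to shape the later full-scale trial, so a flattering score would carry forward.

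**Working it through.** **Inputs from the protocol article.** "We plan to randomize a total of 64 older adults (60 years and older) stratified by sex", split equally, gives 32 per arm. Retention targets are 80% at week 14 and 75% at week 22. Older adults are scored at weeks 5, 14 and 22, and the checklist is at session 5. The sample size rests on the availability of community health worker pairs, so there is no power calculation to reproduce.

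**Calendar (reproduced).** With session 1 in week 1, four weekly sessions, three at two-week intervals and the last four weeks later, sessions fall in weeks 1, 2, 3, 4, 6, 8, 10 and 14. This matches the stated 14 weeks and week 6 for session 5. The first AIM/FIM point (week 5) comes after four sessions and before the fifth.

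**Who is unscored at the retention targets.**
- Week 14: 0.20 × 32 = 6.4, about 6.
- Week 22: 0.25 × 32 = 8.
- Never scored (left before week 5), assuming uniform loss to week 14: 0.20 × 5/14 = 0.071; 0.071 × 32 = 2.3, about 2.
- Lost to the study by the week-6 checklist, same assumption: 0.20 × 6/14 = 0.086; 0.086 × 32 = 2.7, about 3. Anyone who stops sessions but stays in the study adds to this.

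**Effect on the mean score.** Overstatement = share unscored × (mean of stayers − mean of leavers). The documents give no value for the gap, so a range is shown in points on the scale:

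| Assumed gap | Week 14 (0.20) | Week 22 (0.25) | Last available score (0.071) |
|---|---|---|---|
| −0.5 | −0.10 | −0.125 | −0.04 |
| 0 | 0 | 0 | 0 |
| 0.5 | 0.10 | 0.125 | 0.04 |
| 1 | 0.20 | 0.25 | 0.07 |
| 2 | 0.40 | 0.50 | 0.14 |

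The last column assumes that a later leaver's earlier score already reflects their view. If opinion fell only after week 5, the week-14 figure for a 1-point gap lies between 0.07 and 0.20.

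For scale, with an assumed SD of 0.8 the standard error is 0.8/√25.6 = 0.158 at week 14 and 0.8/√24 = 0.163 at week 22. A 1-point gap then gives 0.20/0.158 = 1.3 and 0.25/0.163 = 1.5 standard errors.

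**Bound for a proportion.** Suppose 80% of those scored find the intervention acceptable (an illustration). If everyone without a week-14 score counts as not acceptable, the share of those allocated is 0.80 × 0.80 = 64%. If only the never-scored count so, it is 0.80 × (1 − 0.071) = 74%.

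**Session indicator.** With all 32 as denominator, if 2, 4 or 6 people leave before session 4, the share receiving four sessions is 30/32 = 93.75%, 28/32 = 87.5% or 26/32 = 81.25%. This indicator falls with early leaving, as it should.

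**The case against.** The strongest reply is that the plan sees dropout in several other places. Retention has its own targets and reasons for dropout, participant flow goes into a CONSORT diagram, the session log records early stopping, and supervision notes cover people before they leave. Table 2 sets no success threshold on AIM or FIM, so no stated progression rule turns on a stayers-only mean. The interview plan expressly includes less satisfied people and does not exclude withdrawers. The article is condensed, and handling of missing scores and denominators is normally left to fuller documents.

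Most of this stands, and it limits the point. A reader might infer that all implementation results, fidelity included, are biased upward. The documents do not support that: apart from the checklist, the fidelity indicators do not depend on reaching one fixed visit, and nothing shown removes leavers from their denominator. A reader might also infer from the retention targets that one in five may quit VIDACTIVA out of dislike. Those targets concern remaining in the study; someone who stops sessions can still be assessed at weeks 14 and 22, and people leave for unrelated reasons.

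What the reply does not remove is that the scoring times, the order of scales before interviews and the purpose of the withdrawal interviews are stated choices. Followed as written, they leave the later scores resting on those who remain. Fieldnotes help, but they report through the health workers and not the leavers themselves.

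**Conclusion.** The point holds for the week-14 and week-22 AIM/FIM scores and for the session-5 checklist. It does not hold for the logged fidelity indicators if all 32 are the denominator. About 6 of 32 would lack a week-14 score and 8 of 32 a week-22 score if retention just meets its targets; about 2 of 32 would never be scored if loss is uniform.

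Upward bias is the likely direction but is not established. Its size depends on a gap between stayers and leavers that the documents do not give: 0.20 and 0.25 points for an assumed 1-point gap, about 0.07 on last available scores, zero with no gap, and downward if leavers were the better pleased. The 64% figure is a worst-case bound, not an estimate. This is a worthwhile, low-cost improvement to data collection, and it does not invalidate the pilot.

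**What to change.** 1. Give AIM and FIM when an intervention participant stops sessions or withdraws, within the withdrawal interview already planned.
2. List those interviews in Table 3 as a source for acceptability and feasibility.
3. Reserve some of the 16–20 interview places for people who stopped early.
4. Report AIM, FIM and the checklist with the number scored out of all 32 allocated, and state that the session indicators also use 32.
5. Show the result with unscored people counted as not acceptable only as a sensitivity bound. As a main analysis it would be a debatable imputation, since not all leaving reflects dislike.

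The cost is two short scales in an existing interview and a line or two of reporting. Some leavers will still refuse, and the acceptability figure may become less favourable.

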### Fidelity

We will evaluate the fidelity of the delivery of intervention using a convergent mixed methods approach that includes quantitative indicators and in-depth interviews. The details are displayed in Table 3.

We will analyze various indicators derived from the PEARLS fidelity instrument [43]. Additionally, we will audio record one session (middle session) to evaluate the interaction and relationships of CHWs with older adults, communication skills, and rapport. We will closely evaluate the execution of problem-solving exercises and the scheduling of activities. To facilitate this assessment, we are developing a concise checklist outlining the essential steps of problem-solving exercises.

This multifaceted approach to assessing fidelity will offer a nuanced perspective on the accuracy and integrity of intervention delivery by CHWs, providing rich data that will help guide how to adapt VIDACTIVA intervention and implementation for future RCTs.

### Clinical measures

The preliminary primary clinical outcome will be depressive symptoms. The secondary outcomes will include anxiety symptoms and loneliness.

#### Depressive symptoms

To assess the severity of depressive symptoms, we will use the self-report Patient Health Questionnaire-9 (PHQ-9). We will utilize the Spanish version validated for use in Peruvian population [44, 45]. The PHQ-9 is a 9-item questionnaire. Each item is rated on a 4-point scale. Scores within the range of 5 to 9 indicate mild symptoms, scores between 10 and 14 signify moderate symptoms, a range of 15 to 19 indicates moderately severe symptoms, and scores of > 20 suggest severe depression.

#### Anxiety symptoms

We will evaluate the severity of anxiety symptoms using the Generalized Anxiety Disorder-7 (GAD-7), a validated Spanish version [46]. The questionnaire has 7 items, each with a 4-point scale, with scores between 0 and 21 points. Scores are consider as follows: 0–4 (minimal), 5–9 (mild), 10–14 (moderate), and 15–21 (severe) symptoms [46]. The GAD-7 has demonstrated excellent psychometric properties [47].

#### Loneliness

Loneliness will be assessed using the Three-Item Loneliness Scale (TIL-3) in its Spanish version [48, 49]. Respondents will indicate how frequently they experience feelings of lacking companionship; being excluded; and experiencing social isolation. Participants will provide responses on a 3-point Likert scale, ranging from 1 “hardly ever” to 3 “often.” Individual responses will be summed, with higher scores indicative of greater loneliness. The TIL-3 yields a score ranging from 3 to 9.

### Data analysis

To visualize participant flow, we will employ a CONSORT diagram [50]. For a comprehensive overview, we will provide summary statistics, including means, standard deviations, medians, interquartile ranges, counts, or percentages, for all baseline characteristics, implementation outcomes, and clinical measures.

To provide a comprehensive view of the intervention’s delivery process, we will adopt a mixed-methods approach [42, 51]. This approach will facilitate the creation of a detailed and holistic portrayal of the intervention's implementation. Our plan includes obtaining meta-inferences and creating joint displays for both the implementation and clinical outcomes.

Qualitative data will be organized using MAXQDA software (VERBI GmbH, Berlin, Version 18.2). Qualitative data from in-depth interviews will be analyzed by a multi-disciplinary team. We will examine the initial transcripts and generated preliminary coding categories through an inductive process using the constant comparative method [52]. Through this analytical process, we will identify patterns and commonalities, as well as particularities, that will enhance our understanding of the acceptability and feasibility of the intervention from the perspective of participants, their relatives, CHWs, and other health professionals involved in providing care to older people.

Clinical outcome measures will be summarized for each trial arm at specific time points. We will estimate effect sizes as between-group mean differences for each outcome using linear mixed models post-trial (week 14) and at the end of the follow-up period (week 22). We will present parameter estimates along with 95% confidence intervals. It is important to note that hypothesis testing will not be conducted because this is a pilot trial. All the statistical analyses will be performed using Stata v.17 software provided by StataCorp (College Station, TX).

### Planned interim analysis and stopping rules

No interim analysis has been planned.

### Multiple testing

Given that this feasibility study is exploratory and that there is no hypothesis testing, there will be no adjustment made to the analysis for multiple testing.

### Ethics

The following protocol study has been approved by Universidad de San Martín de Porres (USMP) Institutional Ethical Review Board (reference #948–2023) and Asociacion Benefica PRISMA Ethical Committee (reference #CE0453.23): This trial is registered at Clinical Trials.gov with the identifier NCT06065020. We will obtain written informed consent from the study participants.

## Discussion

We present the justification and methods for the pilot feasibility trial “VIDACTIVA,” a multi-component CHW-lead intervention for Peruvian older adults experiencing depressive and anxiety symptoms. The VIDACTIVA intervention has undergone iterative adaptation from the well-established “Program to Encourage Active, Rewarding Lives” (PEARLS), which has been successfully implemented in the USA over the past 15 years [24, 25, 53].

While PEARLS has indeed shown significant positive outcomes in addressing depressive symptoms and improving quality of life [54], it is essential to recognize the limitations in generalizing its results to low-resource settings and distinct cultural beyond the United States and in the adoption of CHW-led mental health interventions.

The primary objective of this pilot feasibility trial is to bridge these knowledge gaps and prepare for a more extensive and comprehensive trial. The insights gathered throughout this trial will be instrumental in refining our strategies for the main trial. Pilot feasibility testing becomes notably intricate when conducted with populations that have historically been underrepresented in clinical trials, such as older adults [55], and in low-resource settings characterized by significant organizational, cultural, and infrastructural challenges [42]. Explicit attention to culture is needed to obtain health equity [56]. The findings from this study have the potential to inform future adaptations, assessments, and implementations of interventions involving CHWs in urban resource-constrained settings, thereby expanding the mental health workforce to address pressing needs.

While the intervention primarily targets the alleviation of depressive and anxiety symptoms, we recognize that most older adults experience multiple chronic conditions, a phenomenon known as multimorbidity [57]. We anticipate that case discussions during supervision sessions can provide valuable insights into other potential components of a future or refined CHW-led intervention. Furthermore, a key element of the problem-solving component is that older adults themselves select the problems they wish to address and propose solutions. During these exercises, the identified problem may relate to other chronic conditions that older adults are managing (e.g., improving diabetes control). This user-centered approach has the potential to indirectly impact the management of other health conditions, illustrating the broader positive effects of the intervention. This approach aligns with the efforts to integrate mental health with non-communicable diseases care, centering the experience of the people living with mental illness (PAHO) [16, 58].

### Trial status

At the time of manuscript submission, recruitment for this study was ongoing. Recruitment started on 23rd October 2023, is not yet complete and is due to completion on 30th July 2024. This is protocol version 1.2. The trial sponsor is the Universidad de San Martin de Porres.

## Data Availability

Not applicable.

